### Intervention

Suvorexant is a dual orexin receptor antagonist approved by the FDA for the treatment of insomnia. In this study, we will administer 10 mg of suvorexant for 7 nights. Two prior studies from our group suggested that suvorexant could be safely administered to individuals with cocaine use disorder [4] and methamphetamine use disorder [10]. The half-life is about 12 hours on average, and steady-state plasma concentrations occur in 3 days with daily administration [11]. A nurse at the residential programs will administer the medication to participants in the suvorexant group each evening before bedtime, at the same time nightly (around 10 PM), with a medication log to monitor compliance.

All participants will receive TAU, consisting of standard programming from the inpatient facilities, including a combination of individual therapy, group therapy, 12-step meetings, case management, and recreational therapy. Participants in the suvorexant group will receive suvorexant and will be asked to avoid medications listed in the exclusion criteria, including sleep-related medications. Participants in the TAU group will continue their usual medication regimen as prescribed by the inpatient facility staff. A comprehensive list of medications prescribed for each patient will be collected. If possible, statistical analyses will attempt to control for other medication exposure.

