## Methods

### Study Design

We will use an open-label, randomized 2-group design. Participants (n=40) will be randomized to receive 7 days of suvorexant (10 mg) or TAU, consisting of supportive care and symptomatic medication. Figure 1 outlines the schedule of events. Informed consent, eligibility criteria, and baseline sleep data (via actigraphy) will be assessed on day 0 of the study via telephone or video call. Day 0 will ideally occur around 4 days (but within the first week) following admission to the residential program. On day 1 and day 8, participants will be transported to the outpatient treatment research clinic at the Center for Neurobehavioral Research on Addiction (CNRA) to complete the study sessions. At each study session, participants will complete self-report and safety measures (safety measures for the suvorexant group only) followed by administration of the stress reactivity test and then the EEG assessment. Details regarding each of these procedures are provided in subsequent sections. Participants in the suvorexant group will begin receiving the study medication, administered by residential nurses, from day 1 up until day 8 (ie, nights 1‐7). All participants will remain in the residential program until either regular discharge at approximately 30 days (“successful completion”) or early departure (eg, patient-directed discharge or leaving against medical advice). This design captures the critical first 2 weeks of stimulant withdrawal, when sleep disruptions and other withdrawal-related symptoms are typically most pronounced [7].

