### Participants

Participants will be eligible for the study if they are aged between 18 and 65 years and meet the *DSM-5* criteria for a primary StimUD, specifically related to cocaine or methamphetamine. All participants must be fluent in English and capable of fully understanding and providing informed consent for study procedures. These inclusion criteria ensure that participants have the condition of interest and can engage meaningfully with study requirements.

Participants will be excluded if they meet any of the following criteria: (1) diagnosis of an opioid use disorder of any severity; (2) diagnosis of greater than moderate substance use disorder for any substance other than cocaine or methamphetamine; (3) currently receiving medication treatment for withdrawal from any substance; (4) presence of medical conditions that contraindicate the use of suvorexant (eg, severe pulmonary disease, severe cardiovascular disease or clinically abnormal electrocardiogram, severe liver or kidney disease, or sleep disorder—particularly narcolepsy); (5) use of medications known to interact with suvorexant (eg, monoamine oxidase inhibitors, anticonvulsants, haloperidol, phenothiazines, anesthetics, and any sedative); (6) pregnancy or breastfeeding; (7) BMI >30 kg/m^2^ (women only); (8) current *DSM-5* psychiatric disorder or neurological disease requiring ongoing treatment that would make participation unsafe; (9) history of seizure disorder; and (10) history of head injury with loss of consciousness within the past 5 years.

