All models will use distribution families and link functions as appropriate for each outcome (eg, dichotomous outcomes: binomial, with logit link). Longitudinal models evaluating change via interaction terms (eg, treatment × time) will be reduced to main effects if change is unsupported, and both models will be reported. Model fit information criteria (Akaike information criterion; leave-one-out information criterion) will be used to select structural components including multilevel (eg, random intercepts and slopes) and nonlinear terms. Analyses will be performed in R [35] via packages lme4 [36], rstan [37], and brms [38]. Potential confounders will be identified empirically [39,40] (ie, associated with both predictor and outcome) and modeled with and without adjustment; models with unchanged inference will favor parsimony. Sample characteristics (eg, sex, age, and education) will be evaluated as potential confounders. Analyses will be run in parallel using frequentist and Bayesian models. Frequentist results yield the probability of the data (or data more extreme) given the null hypothesis, whereas Bayesian results directly yield the probability of an alternative hypothesis [41,42]. Frequentist models will use *α*=.05 with false discovery rate correction for exploratory tests. Bayesian priors will be weakly informative (β*~* N(0,1); sd~ Half-Cauchy(0,1); correlation matrices ~ LKJ(2)). Bayesian models will be evaluated via posterior probability (PP) threshold guidelines in the literature [43,44], suggesting that PP=75% to 90% indicates moderate evidence, PP=91% to 96% indicates strong evidence, and PP=97% or above indicates very strong to extreme evidence. Posterior predictive checking, scale reduction factors (“rhat”), and effective sample size will be used to evaluate Bayesian assumptions. Evaluation for frequentist models will use graphical evidence and statistical tests. Generalized linear mixed models inherently accommodate outcome values missing at random; other missing values will be handled by imputation or pattern-mixture modeling. Analyses will follow intention-to-treat principles.

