### Conclusions and Future Directions

Notably, this trial was designed as a proof-of-concept study primarily concerned with deriving a preliminary range of plausible effect sizes for mechanistic effects and the effect on treatment completion. The study sample size was selected based on available funding and time to complete the study tasks. Therefore, the results of this study are meant to guide future fully powered trials rather than provide accurate efficacy estimates. A further limitation of this study is the lack of a placebo control and the open-label design. This design introduces potential biases into subjective measures due to participants’ knowledge that they are receiving the treatment. As replication in a larger controlled trial is still needed, a negative finding would not rule out efficacy. Positive findings will also need to be confirmed in a larger sample. A TAU control condition was selected as the next best option and will provide information regarding how add-on suvorexant compares to supportive care and symptomatic medication alone. Critically, the use of several objective measures of main outcomes (actigraphy, HR, BP, cortisol, and EEG) will partially offset the influence of the open-label medication. This translational research approach will be the first mechanism-focused clinical investigation of suvorexant for the treatment of StimUD. FDA approval of suvorexant for the treatment of primary insomnia helps pave the way for rapidly advancing the repurposing of orexin-based therapies for drug addiction treatment.

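### Controlling for on-study medication, when only the suvorexant arm is asked to avoid sleep medication, would depart from the as-randomized comparison, and the add-on wording does not fit the arms

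*Protocol article*

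**What the plan says.** All places are in the protocol article.

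- **Intervention, suvorexant arm:** these participants "will be asked to avoid medications listed in the exclusion criteria, including sleep-related medications".
- **Intervention, TAU arm:** "Participants in the TAU group will continue their usual medication regimen as prescribed by the inpatient facility staff". Study Design describes this arm as "TAU, consisting of supportive care and symptomatic medication".
- **Intervention, analysis:** "If possible, statistical analyses will attempt to control for other medication exposure". No timing of exposure is given, and no model is named.
- **Participants, entry exclusions for both arms:** interacting drugs, a list ending "anesthetics, and any sedative", and anyone "currently receiving medication treatment for withdrawal from any substance".
- **Statistical Analysis Plan:** the aim 1 and aim 2 model holds treatment, time and their interaction, and drops to main effects if change is not supported. "Potential confounders will be identified empirically", by association with both predictor and outcome. Models are fitted with and without adjustment, and the simpler one is preferred when inference does not change. Analyses are to follow intention to treat.
- **Conclusions and Future Directions:** the TAU control "will provide information regarding how add-on suvorexant compares to supportive care and symptomatic medication alone".

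**The concern.** Because the medication rule differs by arm, sleep medication taken during the study is partly a result of assignment. Within TAU it may also be prescribed to those who sleep worst. A model that conditions on it compares the whole suvorexant arm with a selected, unmedicated part of TAU. That is no longer the randomized comparison.

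Sleep is the primary objective, so this is the medication class that matters most. The article says the trial's product is a range of plausible effect sizes for later trials, so a shifted estimate, or one whose contrast is misdescribed, would be carried forward. The add-on label raises the second problem: for sleep medication, the suvorexant arm is asked to go without part of the background that TAU may receive.

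**Working it through.** **1. The plan's own figures.** The article gives no figure for medication use or its effect. Its design analysis (n=36 after attrition; 80% probability of moderate evidence at d=0.26 and of strong evidence at d=0.39) serves here only as a yardstick. It cannot be reproduced uniquely, because the number of time points and the definition of the average effect are not stated. Some readings come close: a time-averaged contrast over 9 points gives 79.4% and 81.6%, and treatment × time over 2 points gives 82.1% and 84.7%. Nothing here disputes it.

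**2. Timing.** Sedatives and withdrawal medication exclude at entry in both arms. After randomization only one arm is asked to avoid sleep medication. A difference between arms would therefore arise mainly after randomization. This follows from reading Participants and Intervention together; neither section says so.

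**3. What adjustment estimates.** Assume sleep medication is taken only in TAU. Let d be the suvorexant effect over no sleep medication, p the share of TAU using it, D how much worse users would sleep than non-users without it, and m the benefit they get from it (d, D and m in SD units). Take the unmedicated mean of non-users as 0.

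- Suvorexant mean: d - pD
- TAU mean: -pD + pm
- As-randomized effect: d - pm
- Adjusted effect (suvorexant minus unmedicated TAU): d - pD
- Shift: (d - pD) - (d - pm) = -p(D - m)

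The documents give none of p, D or m. With p=0.4, D=0.5 (both assumed) and d=0.39:

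| m | As-randomized | Adjusted | Shift |
|---|---|---|---|
| 0 | 0.39 | 0.19 | -0.20 |
| 0.25 | 0.29 | 0.19 | -0.10 |
| 0.5 | 0.19 | 0.19 | 0 |
| 0.75 | 0.09 | 0.19 | +0.10 |

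A wider grid describes prescribing by its correlation r with worse sleep (p 0.25 to 0.75, m 0 to 0.5, r 0 to 0.5, all assumed). It gives shifts from -0.64 to +0.38 SD. In simulations at selected values from this range, the unadjusted contrast recovered the as-randomized effect in every scenario tried.

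**4. Precision.** With 18 per arm, the unadjusted standard error is √(1/18 + 1/18) = 0.333. The adjusted one is √(1/18 + 1/(18(1-p))): 0.360, 0.408 and 0.527 for p = 0.25, 0.5 and 0.75. The ratios are 1.08, 1.22 and 1.58.

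**5. Would the confounder screen pick it up?** If no suvorexant participant takes sleep medication, 5 users among 18 TAU participants are enough for Fisher p<0.05. The probability of that is 48% at p=0.25, 67% at 0.3, 91% at 0.4 and 98.5% at 0.5. This covers the association with arm only; the rule also asks for association with the outcome.

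**6. Which coefficient moves?** The answer depends on coding, which the article does not give. In balanced two-time data with a random intercept, a time-invariant user indicator leaves treatment × time unchanged: 0.378 with and without it in a simulated example, where only the treatment main effect moved. Coding medication as time-varying, or interacting it with time, moved the interaction from 0.378 to 0.239 in the same example. If the model is reduced to main effects, the treatment coefficient is exposed, with D and m then read as averages over the modeled times.

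**7. The add-on wording.** Everyone receives the facility programming, so suvorexant is added to that and to any unrestricted medication. For sleep medication the contrast is suvorexant with other sleep medication avoided, against TAU including any that is prescribed.

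**The case against.** The adjustment is hedged twice, by possibility and by attempt. The stated model has no medication term, intention to treat is declared, and unadjusted models will be reported, so the as-randomized result will be available. The candidate confounders named as examples (sex, age, education) are all pre-randomization. The entry exclusions may keep TAU use of sleep medication low. Which drugs count, when and in which model could properly sit in an analysis plan that is not shown.

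Most of this stands, and it limits the point. A reader might infer that the plan commits to a biased primary analysis, or that adjustment would work against suvorexant by 0.10 to 0.30 SD (the product pD for p from 0.2 to 0.6 and D=0.5). The documents support neither. No medication term is placed in the primary model, and those figures leave out the benefit of the TAU sleep medication, which can cancel or reverse the shift. Nor would every form of adjustment disturb the treatment × time term.

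What the objection does not remove is the selection rule. Reporting both models settles nothing when they disagree, because parsimony decides only when inference is unchanged. The screen on association with arm also points toward a variable that the protocol itself makes differ by arm. The conflict over add-on remains whichever model is used.

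**Conclusion.** The point holds as an unresolved rule, not as a demonstrated bias. The article leaves open an adjustment for medication that its own arm-specific rule would make differ after randomization, and does not say that the as-randomized result prevails if the two models disagree. Such an adjustment departs from intention to treat when medication is coded as time-varying, is interacted with time, or the model is reduced to main effects.

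The shift, -p(D - m), is of unknown size and sign. It vanishes if no TAU participant receives sleep medication or if D equals m. Under some of the assumed values it is comparable with the article's d=0.26 and d=0.39 benchmarks. The result rests on sleep medication being confined to TAU and on post-randomization timing, which is inferred.

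Separately, the add-on description in the Conclusions does not match the Intervention section for sleep medication and must be reconciled with it. No view is taken on which medication rule is right.

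**What to change.** 1. State that the as-randomized model without on-study medication is primary for every aim, and that it stands if an adjusted model differs.
2. Limit adjustment covariates to pre-randomization variables fixed in advance, instead of screening on association with arm.
3. Tabulate on-study medication by arm, with sleep-related medication shown separately.
4. Label any medication-adjusted model as a sensitivity analysis, and state how exposure is coded.
5. In Conclusions and Future Directions, describe the contrast as suvorexant with other sleep medication avoided versus TAU including any prescribed sleep medication. Keep add-on only for shared programming and unrestricted medication.

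The cost is wording in the analysis plan and discussion. Medication lists are already to be collected for each patient, and the article reports that no outcome data are available yet, so the rule can still be set before results are seen.

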### Sleep Assessment

Sleep will be monitored using an activity tracker watch (wGT3X-BT; ActiGraph, LLC) from night 0 to the morning of day 8. Data will be downloaded via the ActiLife software onto a UTHealth Houston computer and securely stored on IT-protected servers. Outcome measures derived from the actigraphy data will include total sleep duration and wake after sleep onset, two widely recognized indicators of sleep quality [12]. To supplement the actigraphy data, participants will complete the National Sleep Foundation Sleep Diary each night to confirm bedtimes and wake-up times for quality control purposes. Additional self-report sleep measures will be collected as described in subsequent sections.

### Study Visit Measures

#### Self-Report and Behavioral Assessments

##### Sleep

The Pittsburgh Sleep Quality Index total summary score will be used to assess baseline sleep quality [13-15]. We will use the Insomnia Severity Index (ISI) [16] and Patient-Reported Outcomes Measurement Information System–Short Form (PROMIS-SF; Sleep Disturbance and Sleep-Related Impairment items) [17] as the main outcome variables. ISI and PROMIS-SF will be assessed on day 5 and day 12 at the laboratory visits to capture changes in sleep over the past 7 days.

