**Objective:**

The primary objective of this randomized open-label clinical trial is to evaluate the effects of suvorexant on sleep, stress, reward processing, and craving during early abstinence in treatment-seeking individuals with StimUD. This proof-of-concept trial represents the first mechanistic evaluation of suvorexant in a residential sample of individuals with StimUD.

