To extend the mechanistic understanding of suvorexant’s effects, we incorporate electroencephalography (EEG) measures of brain function. Two neural markers are of particular interest. First, resting-state alpha power (8‐13 Hz), typically observed over posterior scalp regions during relaxed wakefulness, is sensitive to sleep pressure and may serve as an objective index of daytime neural deactivation [5]. Preliminary data from our group suggest that increased alpha power is associated with poorer subjective sleep quality in people who use stimulants. Second, the reward positivity (RewP) component—an event-related potential elicited by positive prediction errors—indexes reward sensitivity and is often blunted in individuals with substance use disorders [6]. Given the orexin system’s role in (1) modulating mesolimbic dopamine pathways and (2) normalizing sleep architecture, suvorexant may enhance neural responsiveness to nondrug stimuli (potentially both cues and rewards), thereby supporting recovery-related motivational processes.

The primary objective of this translational study is to evaluate the effects of suvorexant on sleep during early abstinence from stimulants—a critical window in which effective withdrawal management may reduce the risk of return to stimulant use. The secondary objective is to examine whether suvorexant will also improve reward processing and reduce stress and craving during early abstinence. By integrating behavioral, subjective, and neurophysiological measures, this investigation represents the first mechanism-focused clinical evaluation of orexin antagonism in StimUD. We hypothesize that suvorexant, relative to treatment as usual (TAU), will improve sleep outcomes during early abstinence (aim 1). We also hypothesize that the secondary outcomes (EEG resting alpha power, acute stress reactivity, non–drug-reward processing, and drug demand) will improve from pretreatment to posttreatment in the suvorexant group compared with the TAU group (aim 2). Finally, we will examine treatment engagement and the effects of the treatment group (suvorexant vs TAU) on posttreatment (days 13‐30) residential program length of stay and completion rates (aim 3). We hypothesize that participants in the suvorexant group, compared with the TAU group, will demonstrate longer posttreatment lengths of stay and higher residential program completion rates.

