There are several strengths and seminal innovations to the current proof-of-concept trial design, but it is not without limitations. This will be the first study to examine the effects of suvorexant during early withdrawal from stimulant use (both cocaine and methamphetamine) in treatment-seeking patients entering residential treatment for StimUD. Furthermore, the well-validated actigraphy-focused sleep assessment will contribute to our understanding of the mechanistic effects of suvorexant in this population. Another first will be leveraging EEG to assess the effects of suvorexant on the waking brain through both resting-state alpha power and the RewP. Finally, this trial will potentially provide effect size estimates of the efficacy of suvorexant regarding the treatment of StimUD, by assessing inpatient treatment completion rates. Despite these strengths, this study will be limited by the open-label design. This could result in the subjective outcomes (eg, sleep quality ratings, stress ratings, and craving scores) being vulnerable to placebo effects, expectancy bias, and demand characteristics. These outcomes will be interpreted cautiously in the statistical analysis. To overcome these concerns, we have included several validated objective outcomes (eg, actigraphy, EEG, and physiological measures), which are less susceptible to participant expectations and will be prioritized when drawing conclusions about treatment effects. Findings from this study will be exploratory and future blinded, placebo-controlled trial designs will establish definitive efficacy.

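### The article contradicts itself on which sleep outcomes lead aim 1, and its lowest evidence label carries an unreported null rate of about 25% per outcome across four or five sleep measures

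*Protocol article*

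**What the plan says.** **Which sleep outcomes lead.** The Methods (Sleep Assessment) state: "Outcome measures derived from the actigraphy data will include total sleep duration and wake after sleep onset". The Methods (Self-Report and Behavioral Assessments, Sleep) then name the ISI and "PROMIS-SF; Sleep Disturbance and Sleep-Related Impairment items) [17] as the main outcome variables". The Discussion (Summary) says subjective outcomes will be read with caution. Of the objective ones it says "which are less susceptible to participant expectations and will be prioritized when drawing conclusions about treatment effects". The Conclusions and Future Directions section also ties the trial's main outcomes to actigraphy and the other objective measures. No section names one primary sleep variable.

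**What is primary.** The Abstract says the primary objective "is to evaluate the effects of suvorexant on sleep, stress, reward processing, and craving during early abstinence". The Introduction says: "The primary objective of this translational study is to evaluate the effects of suvorexant on sleep during early abstinence from stimulants". It places EEG alpha power, stress reactivity, reward processing and drug demand under secondary outcomes.

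**How results are judged.** The Statistical Analysis Plan section runs frequentist and Bayesian models in parallel. The frequentist models use α=.05 "with false discovery rate correction for exploratory tests". The Bayesian results are graded on guidelines "suggesting that PP=75% to 90% indicates moderate evidence", with higher labels from 91% and 97%. No multiplicity rule is stated for the Bayesian models. The same section gives an 80% probability of reaching PP≥75% at d=0.26 and PP≥91% at d=0.39, with n=36. It gives no corresponding probability at d=0.

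**The concern.** The ISI and PROMIS-SF are the sleep measures most exposed to expectancy in an open-label comparison, as the Discussion itself recognises. If one section calls them the main outcomes and another puts actigraphy first, the article leaves room to lead with whichever sleep measure moves.

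Two features widen that room. Aim 1 has several outcomes and no clear multiplicity control, and the entry point of the evidence scale is low. Readers who see an 80% chance of reaching moderate evidence at d=0.26 cannot weigh it without knowing how often the same label appears when there is no effect. The results are meant to guide later trials, so a label that overstates the evidence has consequences even in a proof-of-concept study.

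**Working it through.** **1. The article's own 80% figures.** By normal approximation, 80% probability of reaching a PP threshold c needs d = SE × (z(c) + z(0.80)).

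- PP≥75%: SE = 0.26 / (0.674 + 0.842) = 0.171.
- PP≥91%: SE = 0.39 / (1.341 + 0.842) = 0.179.

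The two figures agree closely with each other. They cannot be rebuilt exactly, because the number of time points and the definition of the average effect are not given. With 18 per arm, AR(1) ρ=0.50 and the N(0,1) prior, two time points with an average effect give 81% and 84%. Nine time points with a mean-level effect give 79% and 81%. The stated figures are attainable and are not disputed.

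**2. Null rate of one label.** With a weak prior, a null effect reaches PP≥c for benefit with probability of about 1−c: 25% at 75%, 9% at 91% and 3% at 97%. Allowing for the N(0,1) prior, the rate is 1 − Φ(z(c) × √(1+SE²)). At c=75% and SE=0.33 this is 1 − Φ(0.674 × 1.054) ≈ 24%, so shrinkage hardly matters.

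**3. Number of sleep outcomes.** Two come from actigraphy (total sleep duration, wake after sleep onset) and one is the ISI. PROMIS-SF adds one score, or two if Sleep Disturbance and Sleep-Related Impairment are scored separately. That makes four or five. Resting alpha power also appears under a Sleep heading but is a secondary outcome, so it is not counted.

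**4. At least one label under a null drug.** For independent outcomes:

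- five at PP≥75%: 1 − 0.75⁵ = 76.3%; four: 1 − 0.75⁴ = 68.4%; two: 1 − 0.75² = 43.8%
- five at PP≥91%: 1 − 0.91⁵ = 37.6%; at PP≥97%: 1 − 0.97⁵ = 14.1%
- five at two-sided p<.05: 1 − 0.95⁵ = 22.6%

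The article gives no correlation between sleep outcomes, so r is an assumption. The rows with r>0 come from simulated equicorrelated normal statistics (1,000,000 draws).

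| Assumed r | Five, PP≥75% | Five, PP≥91% | Five, PP≥97% | Five, p<.05 | Two actigraphy, PP≥75% |
|---|---|---|---|---|---|
| 0 | 76.3% | 37.6% | 14.1% | 22.6% | 43.8% |
| 0.3 | 64.4% | 31.3% | 12.4% | 20.9% | 40.5% |
| 0.5 | 56.6% | 26.9% | 10.7% | 18.3% | 38.0% |
| 0.7 | 48.2% | 22.0% | 8.7% | 14.8% | 35.0% |
| 0.9 | 37.6% | 15.8% | 6.0% | 10.2% | 30.6% |

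The five-outcome figure at PP≥75% falls below 50% at r of about 0.66. Block structures (0.3 to 0.5 within actigraphy, 0.6 to 0.7 within self-report, 0.1 to 0.3 between) give 58% to 64%.

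**5. Not upper bounds.** If the interaction is unsupported, a main-effects model is also reported. If the two statistics were independent, the per-outcome null rate would rise from 25% to 0.25 + 0.50 × 0.25 = 37.5%, when the fallback is used only for PP between 25% and 75%. It would rise to 0.25 + 0.75 × 0.25 = 43.8% if the fallback is used whenever benefit falls short of 75%.

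**The case against.** The strongest reply is that the trial has no success rule to inflate. The Statistical Analysis Plan section presents the study as estimation rather than definitive testing, the Discussion calls the findings exploratory, and the Conclusions require confirmation in a larger sample. The PP bands are descriptive labels taken from cited guidelines. This stands: no sleep outcome formally decides the trial. It does not remove the point, because the Introduction states directional hypotheses and the Discussion speaks of drawing conclusions.

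A reader might infer that a null drug will probably yield a positive sleep finding. The document does not support that as a general statement. It requires all five outcomes to count, PP≥75% to be read as positive, and a correlation below about 0.66. If objective measures come first, as the Discussion says, only two measures lead and the chance is 31% to 44%.

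A reader might also infer that the sleep tests are certainly uncorrected. That is unsettled. Aim 1 carries a stated hypothesis, which suggests it lies outside the FDR rule, but the Discussion's description of the findings as exploratory could bring it inside.

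It is also fair to say that the ISI and PROMIS-SF may be meant as the main outcomes among the self-reports only. They follow a sentence giving the PSQI to baseline, and Sleep Assessment treats questionnaires as additional to actigraphy. The text does not state this limit, so the wording still needs repair.

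Finally, PP 75% converts to a two-sided p of 2 × (1 − 0.75) = 0.50 under a flat prior, but the like-for-like figure is a one-sided rate of 25%, and the frequentist result will be shown alongside.

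**Conclusion.** The point holds as one of consistency and labelling. The article conflicts on whether self-report or objective sleep measures lead, and on whether one domain or four are primary. FDR coverage of aim 1 is unclear, and the Bayesian reading has no multiplicity rule. The moderate label has a null rate of about 25% per outcome, which is not reported beside the 80% figure.

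With a null drug, at least one of five sleep outcomes reaches PP≥75% for benefit in 76% to 57% of trials for r from 0 to 0.5, 48% at r=0.7 and 38% at r=0.9. For at least one of five at p<.05 without correction, the range is 23% to 10% over r from 0 to 0.9. These figures rest on an assumed common correlation, on PROMIS-SF giving two scores, and on a single model per outcome. They describe how often a label would appear by chance, not the error rate of a decision rule, since the article contains none.

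**What to change.** - Name one actigraphy measure as the aim 1 primary outcome; the sponsor chooses total sleep duration or wake after sleep onset.
- In the self-report Sleep section, relabel the ISI and PROMIS-SF as secondary self-report outcomes, in line with the Discussion and Conclusions.
- Align the Abstract's objective with the Introduction, so that sleep alone is primary.
- State that FDR control applies to all other sleep outcomes and to the aim 2 outcomes.
- Report the null rate of each PP band (about 25%, 9% and 3% per outcome) beside the 80% figures and again with the results.

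A rule restricting claims to PP≥97% is not needed. With the implied SEs of 0.171 and 0.179, 80% probability of reaching it would require d of (1.881 + 0.842) × SE, about 0.47 to 0.49, against the stated 0.26 and 0.39. That would impose a confirmatory bar on an estimation study.

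The cost is wording. The downside is that fewer outcomes can be headlined as evidence. At submission in September 2025, 8 of 40 participants were enrolled and the Results section reports no outcome data available, so the choice could then still be made prospectively.
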